### Self-Reported Measures

#### Movement-Specific Reinvestment Scale Adapted for Gait

The MSRS is a questionnaire that measures a person’s inclination for conscious control. People after stroke have shown to have greater propensity to conscious processing compared with the age-matched, nondisabled population [49,50]. In this study, an adapted version of the MSRS specific to gait is used. Adapted versions of the MSRS have been used before, for example, for putting movements in golf [51,52]. The MSRS contains one factor related to conscious control (conscious motor processing) and one related to self-consciousness about movement (movement self-consciousness). Each factor of the MSRS comprises 5 statements, such as “I try to think about my movements when walking” (conscious motor processing) and “I am concerned about what people think about me when I am walking” (movement self-consciousness). The statements will be assessed with binary response (yes/no) [40]. The MSRS will be measured at baseline (T0) to describe the population and over time (T0, T1, and T2) to assess how much gait-related conscious processing takes place.

#### Verbal Protocol

To assess the amount of explicit knowledge, a verbal protocol questionnaire as used in Orrel et al will be administered after the 3-week intervention [22]. Explicit knowledge is assessed by examining the number of explicit rules that the participant uses during walking. Participants will be asked to report any “rules, methods, or techniques” that they have thought about or used and that have improved or impaired their walking performance. A rule is defined as any statement containing at least one of the following aspects: a movement or position of one limb, a movement or position of one joint, a velocity of a limb movement, an angle or direction of a joint or the spine, or the placement of the walking aid. Each statement containing a single limb, joint, or other body part will be counted as 1 rule. If a statement contains 2 (or more) different limbs, joint and body parts, or different directions or angles, they are counted separately (eg, “I tried to lift my foot and put it more forward.”). Statements are excluded if they are irrelevant to walking performance or do not refer to technical aspects about walking (eg, “More concentration needed.”). The answer to the verbal protocol will be screened by 2 independent researchers who will be blind to the experimental condition. Their agreement will be investigated using a correlation coefficient (or ICC).

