### Sample Size

The sample size calculation is based on a randomized controlled trial with equal group sizes and “walking speed” (10-meter walking test, 10MWT) as a primary outcome measure [30]. The power is set at beta=.80, the significance level at alpha=.05, and a standard deviation of 0.23 m/s [31]. To demonstrate a significant change in walking speed, the minimal clinically important difference (MCID) is used and set at a minimum change of 0.16 m/s [32,33]. The calculations resulted in a minimum group size of 33 participants per group. Taking into account that 20% (7/33) of participants may be lost during (dropout) and after the intervention (loss to follow-up), this study aims to recruit 40 participants per group.

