### Process Evaluation

To gain an insight into the process-related factors that may have influenced the effectiveness of the 3-week analogy learning walking intervention, a process evaluation will take place along the study [55]. Data will be collected to (1) asses to what extent the therapists delivered the interventions as intended (fidelity), (2) explore the therapists’ opinions and experiences about the interventions with regard to the feasibility and possible effects, and (3) explore the patients’ opinions and experiences about the interventions with regard to the feasibility. Table 2 represents the data collection methods used to assess the different aspects of the process evaluation. For both groups, the provided instructions will be documented and evaluated in the therapists’ logs. In addition, short questionnaires will be used to administer the therapists’ and participants’ opinions about the gait training after the completion of the 3-week intervention. To explore the extent to which the interventions were implicit or explicit in nature, the verbal protocol will be assessed. Evidence indicates that implicit learning is typically characterized by the less accumulation of explicit rules compared with explicit learning [24,56].

To monitor the integrity of the intervention, self-reported (subjective) and audio-recorded (objective) data will be evaluated. First, all therapists are required to self-report any deviations from the treatment protocol or other incidents during the session in a log after every session. All instructions used during therapy sessions will be recorded in the therapists’ and patients’ logs. Furthermore, patients can use the log to write down any possible events that might have occurred during unguided therapy. The patient log is, therefore, only used as a reminder for unguided therapy and as a communication tool between therapists and participants. Second, 10 gait trainings will be randomly selected (5 implicit and 5 explicit interventions) and audio recorded. Both self-reported and audio-recorded data will be screened to evaluate whether the intervention was delivered according to the protocol.

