### Implicit Motor Learning

Scientific evidence describes that implicit learning is typically characterized by robust dual-task performance, durable performance over time, and less accumulation of explicit rules [24,56]. The dual-task measure and the 1-month follow-up session were specifically chosen with respect to these implicit characteristics. First, walking while concurrently carrying out a secondary (tone counting) task [48] places high information-processing demands on the learners. In contrast to explicit learners, implicit learners showed that performance was not disrupted in dual-task conditions, which indicates that they may be able to free up attentional resources to perform the secondary task [24]. We therefore predict that the implicit condition will remain stable under secondary task burden. For this reason, implicit learning may be particularly beneficial for those who experience cognitive impairments that are commonly seen in people after stroke.

Then, a recent study by Tse et al [25] found performance improvements after a 2-day separation; however, they recommended to include a longer separation to test skill consolidation. This study will therefore evaluate performance after the 1-month follow-up period. It is hypothesized that performance improvements in the implicit group will remain robust over a longer period (1-month follow-up). To make statements about long-term effects within rehabilitation, it may be desirable for future studies to include even longer follow-up periods (>3 months). Finally, a verbal protocol will be assessed because it is hypothesized that participants within the implicit learning group will report fewer explicit rules than the control group, which would be in line with the findings of earlier studies [23,24]. Even though the starting point of the explicit intervention is to use many verbal explicit instructions and provide more details on the motor performance, the exact number of explicit rules will be tailored to the ability of the patient to process these rules. Therefore, in practice, some patients might receive higher numbers of explicit rules than others. Still, we hypothesize that the explicit group will require more explicit rules compared with the implicit group.

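### The plan allows agreement between the two raters of explicit rules to be judged by a correlation, which does not register a systematic difference between them

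*Protocol article*

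**What the plan says.** The Verbal Protocol section defines the measure as a count: "Explicit knowledge is assessed by examining the number of explicit rules that the participant uses during walking". It sets out when one statement yields more than one rule: "If a statement contains 2 (or more) different limbs, joint and body parts, or different directions or angles, they are counted separately". The answers are "screened by 2 independent researchers who will be blind to the experimental condition", and the section then says: "Their agreement will be investigated using a correlation coefficient (or ICC". It names neither the kind of correlation nor the form of ICC.

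The count is used in two ways. Under Process Evaluation it helps to describe the contrast between the conditions: "To explore the extent to which the interventions were implicit or explicit in nature, the verbal protocol will be assessed". In the Discussion (Implicit Motor Learning) it carries a directional hypothesis that "participants within the implicit learning group will report fewer explicit rules than the control group".

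**The concern.** The stated aim is agreement on a number, but the first statistic named is one of association. A correlation asks whether the raters rank and space the participants alike. It does not ask whether they arrive at the same count.

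The counting rule leaves room for a systematic difference. A statement about a single body part counts as one rule, yet different directions or angles are counted separately. The article's own example, about lifting the foot and placing it further forward, has one body part and two movements. One rater may habitually split such statements more than the other.

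At stake is how far readers can trust the reported number of rules per arm and the statement that the raters agreed. Both bear on whether the implicit and explicit conditions really differed.

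**Working it through.** **Inputs.** From the article: two raters, blind to condition; the rated quantity is a count; planned recruitment is 80 in total (Sample Size: "this study aims to recruit 40 participants per group"). The article gives no SD of rule counts, no expected agreement and no threshold, so there is no figure to reproduce. The SDs, means and excesses below are assumptions.

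**Step 1: constant excess.** Let rater A give x, with between-participant SD s, and let rater B give x + b, with no other error. Then r = 1 for any distribution of counts that vary. In large samples the two-way absolute-agreement, single-rater ICC is

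ICC(A,1) = s² / (s² + b²/2)

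| Assumed SD s | b = 1 | b = 2 | b = 3 |
|---|---|---|---|
| 1 | 1/1.5 = 0.67 | 1/3 = 0.33 | 1/5.5 = 0.18 |
| 2 | 4/4.5 = 0.89 | 4/6 = 0.67 | 4/8.5 = 0.47 |
| 3 | 9/9.5 = 0.95 | 9/11 = 0.82 | 9/13.5 = 0.67 |

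In every cell r = 1.00, although the raters match on no participant. The consistency ICC is also 1.00 in every cell.

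**Step 2: check from ANOVA mean squares.** Take 80 participants with counts spread evenly over 0 to 7 (mean 3.5, SD 2.31). For +1, +2 and +3 rules, ICC(A,1) is 0.91, 0.73 and 0.54, with r = 1.00 throughout. The formula agrees: for +1, 5.32/(5.32 + 0.5) = 0.91.

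**Step 3: proportional excess.** With the same counts and rater B at 1.5 or 2 times rater A, r is still 1.00. ICC(A,1) is 0.78 and 0.55, and the consistency ICC is 0.92 and 0.80.

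**Step 4: varying excess.** Let counts be Poisson with mean 3 (variance 3). Let rater B add 1, 2 or 3 rules at random (mean 2, variance 2/3).
- r = √(3/(3 + 2/3)) = 0.90
- Consistency ICC = 3/((3 + 3.67)/2) = 3/3.33 = 0.90
- ICC(A,1) = 3/(3.33 + 2²/2) = 3/5.33 = 0.56

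The averages over 2,000 simulated sets of 80 are 0.90, 0.90 and 0.56. Here r is below 1 because of the random part of the excess. The average shift of 2 rules does not enter it.

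**Step 5: effect on the comparison of arms.** Let the arm means be m₁ and m₂ on rater A's counts.
- Constant excess: (m₁ + b) − (m₂ + b) = m₁ − m₂. The difference, its SD and a test of the difference do not change; each arm's reported mean rises by b.
- Proportional excess: k·m₁ − k·m₂ = k(m₁ − m₂). With k = 1.5, the difference in rules is 1.5 times as large.

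**The case against.** The strongest reply is that the ICC is already in the sentence. An ICC is a kind of correlation coefficient, so the bracket may name the kind intended, and the article nowhere says Pearson. This stands in part. The plan permits the unsuitable statistic but does not commit to it. As written, though, a correlation alone would satisfy the sentence.

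Second, the form of ICC and its interval are details that a condensed article may leave to a fuller document. This is fair, and their absence is not the complaint. The form matters only for the remedy, because writing ICC alone would still admit a consistency version that is blind to a constant shift.

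Third, the constant-excess illustration is stylised. Splitting adds rules only where a participant offers a statement that can be split, so someone who reports no rules gains none. The article also defines a rule, gives an example and lists exclusions, which should limit drift between raters. This stands: the table shows a property of the statistic, not a forecast of how these raters will differ.

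Fourth, the hypothesis compares arms and the raters are blind, so a constant excess does no damage to that comparison. For the contrast alone, consistency is arguably the relevant property. This also stands, and it narrows the harm. It does not rescue the statistic for its stated purpose, which is agreement.

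Finally, delivery is also checked through therapist logs, audio recordings and a therapist questionnaire, and Table 2 does not list the verbal protocol among the fidelity measures. The rule count is therefore not the only evidence that the conditions differed.

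**Conclusion.** The point holds as a minor one. The article sets out to examine agreement and accepts a statistic that cannot show a systematic disagreement. That property of r does not depend on the assumed figures. The size of the gap does: under a constant excess of 1 to 3 rules and an SD of 1 to 3 rules, the absolute-agreement ICC lies anywhere from 0.95 down to 0.18 while r is 1.00.

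A reader might infer two stronger claims that the document does not support. One is that r is exactly 1.0 whenever one rater counts more on every participant. That needs a constant or proportional excess and no other error; with a varying excess r was about 0.90. The other is that the comparison of arms would be biased. Under blinded rating, a constant excess leaves it unchanged. What can mislead is the agreement claim, the rule counts reported per arm and, under a proportional excess, the size of the arm difference in rules. The primary outcome is not touched.

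**What to change.** Replace the sentence on agreement with, for example: *Agreement between the two raters on the number of explicit rules will be reported as a two-way absolute-agreement ICC with 95% CI, together with the mean difference between raters.* Remove the correlation option.

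The cost is one sentence. Two researchers already screen the answers, so no new data or extra rating is needed. The mean difference also tells the reader, in rules, how far one rater tends to exceed the other, which no single coefficient conveys.

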#### Stroke and Aphasia Quality of Life Scale

The *Stroke and Aphasia Quality of Life Scale (* SAQOL-39) is assessed at baseline and after the intervention to measure the health-related quality of life [53]. The questionnaire contains 39 items and is developed for people after stroke and is feasible to use for people with aphasia. The SAQOL-39 is a short version of the original SAQOL (53 items) and has shown to be an acceptable, reliable, and valid measure of the health-related quality of life [53].

#### Global Perceived Effect

The *Global Perceived Effect* scale is a reliable method to assess the participant’s satisfaction and will be used to evaluate the participant’s perception of the intervention [54]. The Global Perceived Effect scale will involve the following question: To which extent did your walking ability change over the last three weeks? The question will be scored on a 7-point Likert scale from “completely improved” to “completely deteriorated.”

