## Methods

### Study Design

The study adopts a randomized, controlled, single-blinded study design in people suffering from stroke in the chronic stage of recovery. The study has been approved by the local ethics committee METC-Z in Heerlen, the Netherlands (NL number: NL.60338.096.16, Ethics nr: 17-T-06). After baseline measures, eligible participants will be randomized to the implicit or explicit condition (T0). Outcome assessments will take place directly after the intervention (T1) and again one month later (T2).

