#### Training of Therapists and Treatment of Participants

An intervention guideline is developed that outlines how the treatments (implicit and explicit conditions) should be delivered. The main aim of the intervention is to improve the quality of walking performance in people after stroke. The basic principle of the intervention guideline is based on the definitions of implicit and explicit motor learning by Kleynen et al [11]. For the purpose of this study, we strive to create the largest contrast between the conditions as possible. The main characteristics and differences in instructions, and feedback of the practice between interventions are described in Figure 1. Both conditions will always be applied to an extent that is feasible for the participant, and training will therefore always be tailored to the participant’s abilities within the given boundaries of the condition. Similar situations will be adopted in both conditions with regard to the “organization” of the training, for example, use variation in the (analogy) instructions and practice of the motor skill.

The chosen intervention period was based on a preliminary study of Kleynen et al [28] that demonstrated that 3 weeks was a feasible period to develop and practice analogies with people after stroke. All participants will receive 9 training sessions in a 3-week intervention period, that is, 3 training sessions per week (Figure 2). Each training session takes place at the home of the participants and lasts for 30 min. Participants were asked to use the instructions in daily life (unguided therapy) and after the 3-week intervention period. To standardize the training content as much as possible, the therapists involved in the study will be trained before the start of the study. During 5 standardization training sessions, the intervention guideline will be discussed, explicated, and the therapists will be trained with the help of example cases. During the trial, therapists will attend 3 evaluation sessions to discuss the progress of the study and possible cases or difficulties they may experience during the intervention.

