**General outcome measures**			
	Movement Specific Reinvestment Scale	T0, T1, T2	Personal factors
	Verbal protocol	T2	N/A^b^
	Stroke Specific Quality of Life Scale	T0, T2	Participation level
	Global Perceived Effect scale	T2	N/A

^a^ICF: International Classification of Functioning, Disability, and Health.

^b^N/A: not applicable. The ICF level is not applicable for the Verbal Protocol and Global Perceived Effect Scale as these measures do not examine health or disability but evaluate the intervention.

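### The Global Perceived Effect question looks back three weeks but is scheduled only one month after training, so its wording, its time point and its stated purpose conflict

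*Protocol article*

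**What the plan says.** The section on the Global Perceived Effect scale gives the question in full: "To which extent did your walking ability change over the last three weeks". It is answered on a 7-point scale. The same section says that the scale "will be used to evaluate the participant’s perception of the intervention", and the footnote to Table 1 says of this scale and the verbal protocol that "these measures do not examine health or disability but evaluate the intervention".

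That section names no visit. The only place that does is the row in Table 1, which reads "Global Perceived Effect scale T2 N/A".

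The visits are defined under Study Design: "Outcome assessments will take place directly after the intervention (T1) and again one month later (T2"). The training is described under Training of Therapists and Treatment of Participants: "All participants will receive 9 training sessions in a 3-week intervention period". The same paragraph adds: "Participants were asked to use the instructions in daily life (unguided therapy) and after the 3-week intervention period".

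**The concern.** Each statement is clear alone, but together they do not work. The purpose is to learn how participants judge the intervention. The wording limits the answer to the preceding three weeks. The schedule puts the question at a visit where those three weeks come after the supervised training.

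What is at stake is the meaning of one secondary outcome. A participant who walked better by the end of training and has been stable since would, taking the question at its word, report no change. A participant who lost some of the gain would report deterioration even if still better than at baseline. Others may ignore the time limit and answer about the training. The responses would then hold two different quantities that cannot be separated afterwards. The scale has no other scheduled administration to fall back on.

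**Working it through.** The plan gives no computed figure on this point, so there is none to reproduce. The check is date arithmetic.

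**Inputs**
- Training: 3 weeks, so 3 × 7 = 21 days, set as day 0 to day 21 (Training of Therapists and Treatment of Participants).
- T1: directly after training, taken as day 21 (Study Design).
- T2: one month after T1. The article does not give this in days; I assume m = 28 to 31.
- Look-back of the question: 3 weeks = 21 days (Global Perceived Effect).

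**Formulas**
- T2 = 21 + m
- Window opens at T2 − 21 = m
- Overlap with training = max(0, 21 − m)
- Gap between end of training and start of window = m − 21

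**Results**

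| Question asked at | Day of visit | Window (days) | Training days inside | Gap after training |
|---|---|---|---|---|
| T2, m = 28 | 49 | 28–49 | 0 of 21 | 7 days |
| T2, m = 30 | 51 | 30–51 | 0 of 21 | 9 days |
| T2, m = 31 | 52 | 31–52 | 0 of 21 | 10 days |
| T1 | 21 | 0–21 | 21 of 21 | none |

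**Sensitivity.** The window at T2 would reach into training only if T2 fell less than 21 days after training ended, which is incompatible with a one-month interval. A ninth session before day 21, or a T1 visit some days late with T2 still a month after it, would only widen the gap.

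**Direction of bias.** Assume literal answers and consider two cases.
- Both arms keep their gains. Both arms answer that nothing changed, and a true difference in perceived benefit from training is hidden.
- The implicit arm keeps its gain and the explicit arm loses some. A difference appears, but it reflects loss after training and could exceed the difference in perceived training benefit.

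The Discussion (Implicit Motor Learning) hypothesises that gains in the implicit group will last to one month, so the second case cannot be set aside. The sign of any distortion is therefore open.

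**The case against.** Five arguments can be made on the other side.

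1. **The table may be the slip.** The time point rests on one table cell. Other rows of the same block also sit loosely with the text. The verbal protocol "will be administered after the 3-week intervention" according to its own section, and the SAQOL-39 is placed at baseline and after the intervention, yet Table 1 gives T2 as the only post-baseline time for both. Table 1 also names the quality-of-life scale differently from the text. If the entry should be T1, the window matches the training exactly. This stands as a reason not to present T2 as a deliberate choice. It does not remove the conflict, because the article as written gives T2 and nothing else.

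2. **The window is not empty of intervention.** Participants were asked to keep using the instructions after the three weeks, so a look-back at T2 covers that unguided use. This stands. A reader might infer that the question misses the intervention altogether. The documents support only the narrower statement that it misses the whole 3-week supervised programme.

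3. **Participants may not answer literally.** At a trial visit, some will take the question to mean the training. That is plausible, but it makes the answers a mixture and does not restore the intended meaning.

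4. **Attenuation is not shown.** A reader might infer that the mismatch pulls the difference between arms toward zero. That would need similar retention in both arms, which the protocol's own hypothesis does not assume.

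5. **The scale is secondary.** The research question, the sample size and the primary outcome do not depend on it, and the Data Analyses section names no specific test for it. A separate patient questionnaire collects opinions after the 3-week training, although Table 2 ties it to feasibility, so it is not a substitute for perceived change in walking. This limits the importance of the point but not its correctness.

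**Conclusion.** The inconsistency is real. Followed as written, the plan asks a question whose three-week window opens 7 to 10 days after training and holds 0 of 21 training days and none of the nine supervised sessions, while the article says that the scale evaluates the intervention. Taken literally, it measures change during follow-up with unguided use of the instructions. In practice it probably yields a mixture of that and recall of the training.

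The conclusion assumes that a month means 28 to 31 days and that the Table 1 entry was put into practice. If it was, every participant who completes the T2 assessment is affected, out of a recruitment target of 2 × 40 = 80. If the entry is an error for T1, no answers are affected and only the table needs correcting. The documents do not settle which is the case.

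A reader might go further and conclude that the outcome can never be reported as perceived effect of the training. The documents do not support that, because it would require both that T2 was used and that everyone answered literally. The point is minor to moderate and confined to one single-item secondary outcome. The primary outcome, walking speed, and the sample size are unaffected.

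**What to change.** First establish from the assessment forms when the scale was given and with what wording. Then align Table 1 and the Global Perceived Effect section in one of two ways:

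- give the question at T1 with its present wording and correct the time point in Table 1; or
- keep T2 and ask about change in walking ability since the start of the walking training.

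The first captures perceived change over the supervised training. The second captures perceived change over training and follow-up together, and the report should say so. Answers collected under a different wording or time point should be reported separately, with the wording and visit stated, and not pooled with the rest. The verbal protocol and quality-of-life rows of Table 1 can be checked against their text sections at the same time.

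The cost is one table entry or one line on the assessment form. No extra visit is needed. The only real loss is that answers already collected under another combination are not directly comparable with later ones.
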